# Prevention of Recurrent Spontaneous Preterm Delivery Using Probiotics (Clostridium butyricum, Enterococcus faecium, and Bacillus subtilis; PPP Trial): Protocol for a Prospective, Single-Arm, Nonblinded, Multicenter Trial

**DOI:** 10.2196/59928

**Published:** 2024-09-09

**Keywords:** clostridium, multicenter open label trial, preterm delivery, probiotics, recurrent spontaneous preterm delivery, prospective single-arm, spontaneous preterm delivery, infection, oral probiotics, pregnant women, pregnant, pregnancy, neonates, preterm births, systematic review, meta-analysis

## Abstract

**Background:**

The rate of recurrent spontaneous preterm delivery (sPTD) ranges between 27% and 34% and is 22.3% in Japan. Although it currently remains unclear whether probiotics prevent sPTD, retrospective studies recently reported a reduction in the rate of recurrent sPTD with the administration of probiotics including *Clostridium* spp., which induce regulatory T cells that play an important role in maintaining pregnancy.

**Objective:**

The objective of this trial is to evaluate the preventative effects of available oral probiotics, including *Clostridium butyricum*, on recurrent sPTD.

**Methods:**

This is a prospective, single-arm, nonblinded, multicenter trial in Japan. The sample size required for this trial is 345 pregnant women with a history of sPTD, considering a clinically significant reduction in the relative risk of 30% (risk ratio=0.7). The primary endpoint is the rate of recurrent sPTD at <37 weeks of gestation. The secondary endpoints are the rate of sPTD at <34 weeks of gestation, the rate of recurrent sPTD at <28 weeks of gestation, the ratio of intestinal *Clostridium* spp. (detected by next-generation sequencing), and bacterial vaginosis (using the Nugent score).

**Results:**

The trial procedures were approved by the Clinical Research Review Board of Toyama University Hospital (SCR2020008) on March 31, 2021. The trial was registered on the Japan Registry of Clinical Trial website on April 28, 2021. Recruitment began on May 1, 2021, and the trial is estimated to finish on March 31, 2025.

**Conclusions:**

The findings will clarify the rate of recurrent sPTD following probiotic administration including *Clostridium butyricum*. Outcomes from this trial will inform clinical practice and guide future randomized controlled trials.

**Trial Registration:**

Japan Registry of Clinical Trials jRCTs041210014; https://jrct.niph.go.jp/latest-detail/jRCTs041210014

**International Registered Report Identifier (IRRID):**

DERR1-10.2196/59928

## Introduction

According to a systemic analysis, 13.4 million (12.3-15.2 million) live neonates were estimated to be delivered as preterm births (<37 weeks) in 2020 (9.9% [9.1%-11.2%] of all births) worldwide [1]. In addition, the number of neonate (aged 0 days to 27 days) deaths due to preterm birth complications is estimated at 938,000 [2]. Preterm neonates are at an increased risk of mortality and morbidity, such as sepsis, periventricular leukomalacia (PVL), intraventricular hemorrhage (IVH), cerebral palsy, seizures, bronchopulmonary dysplasia (BPD), necrotizing enterocolitis (NEC), feeding difficulties, and visual or hearing disorders [3]. Between 30% and 35% of preterm births are indicated, 65% to 70% are spontaneous preterm deliveries (sPTD) [4], and the rate of recurrent sPTD ranges between 27% and 34% [5]. In Japan, the rate of recurrent sPTD was recently reported to be 22.3%, based on real-world data from 2014 to 2016 [6].

sPTD is caused by multiple pathological processes [4,5,7], with intra-amniotic inflammation or infection being the main cause [7-9]. As the clinical characteristics of sPTD, severe intra-amniotic inflammation and infection were more frequent in the earlier weeks of gestation [8-10]. Since preterm labor, the preterm premature rupture of membranes, and cervical insufficiency develop due to the collapse of the intrauterine environment, such as by inflammation or infection, it is difficult to avoid sPTD after the appearance of clinical symptoms. Therefore, precautions are needed to prevent sPTD in pregnant women at a high risk of sPTD starting in the first trimester or before pregnancy.

In 2013, alliums (garlic, onion, leek, and spring onion) and dried fruits (raisins, apricots, prunes, figs, and dates) were reported to be associated with a decreased risk of sPTD [11]. In another prospective cohort study reported in 2019, intake of fermented food, such as miso soup, yogurt, and soybeans, before pregnancy significantly reduced the risk of early sPTD at <34 weeks [12]. According to a large-scale, epidemiological, observational, cohort study conducted in Norway, the consumption of probiotic milk during early pregnancy was correlated with a lower risk of preterm delivery (adjusted odds ratio 0.79, 95% CI 0.64-0.97; *P*=.03) [13]. As one of the pathological characteristics in the intestinal flora of pregnant women with sPTD, the abundance of *Clostridium* spp. was significantly lower than in pregnant women who delivered at term [14]. These findings of large-scale epidemiological studies and the specificity of the intestinal flora strongly suggest the potential of prebiotics or probiotics to improve the intestinal microbiota and prevent sPTD.

On the other hand, clinical studies using probiotics have not been sufficiently powered to prevent sPTD [15]. The findings of a systematic review and meta-analysis showed that the consumption of probiotics or prebiotics during pregnancy did not affect the risk of sPTD [16,17]. However, the types of probiotics or prebiotics used in each trial varied. Moreover, the initiation of their administration was not constant, or the characteristics of pregnant women at risk of sPTD differed. Therefore, findings on the efficacy of probiotics to prevent sPTD have been inconsistent.

*Clostridium* spp. induce the production of regulatory T (Treg) cells [18], which are essential for the maintenance of pregnancy [19-22]. Since the abundance of *Clostridium* spp. is significantly reduced in sPTD cases [14], the number of Treg cells produced may be insufficient to maintain pregnancy. Therefore, probiotics including *Clostridium* spp. have the potential to prevent sPTD in women at risk of sPTD. In 2 retrospective cohort studies, probiotics including *Clostridium* spp. reduced the recurrence of sPTD. One study showed that the rate of preterm delivery at <32 weeks of gestation was significantly reduced in pregnant women at a high risk of sPTD [23], while the other demonstrated that the rate of recurrent sPTD was significantly reduced (9.8% vs 30.1%, *P*=.002) by probiotics including *Clostridium* spp [24].

Based on this clinical and pathological background, we are planning a phase 3, prospective, single-arm trial to confirm the preventative effects of probiotics, including *Clostridium butyricum*, on sPTD in pregnant women with a history of sPTD. This trial will evaluate the rate of recurrent sPTD based on that reported in a perinatal registration database from the Japan Obstetrics and Gynecology Society for the perinatal center (22.3%) [6], which covers approximately 25% of deliveries in Japan.

## Methods

### Trial Design

The Prevention of Recurrent Spontaneous Preterm Delivery by Probiotics (PPP) trial is designed as a prospective, single-arm, nonblinded, multicenter clinical trial to confirm the prevention of sPTD by oral probiotics in pregnant women with a history of sPTD. In Japan, 31 hospitals are participating, and the trial is scheduled to run from April 1, 2021, to March 31, 2025 (registration period was from June 1, 2021, to March 31, 2024.) The design of the trial is summarized in Figure 1. This trial will be performed according to the ethical principles originating from the Declaration of Helsinki and the Clinical Trial Act.

**Figure 1 figure1:**
[figure not shown]
A summary of the design of the Prevention of Recurrent Spontaneous Preterm Delivery by Probiotics (PPP) trial. After informed consent, the oral administration of probiotics, including *Clostridium butyricum* (10 mg/tablet), *Enterococcus faecium* (2 mg/tablet), and *Bacillus subtilis* (10 mg/tablet), is initiated at 10-14 weeks. BFS: Bristol Stool Form Scale; CRP: C-reactive protein; CSS: constipation scoring system; NGS: next-generation sequencing; WBC: white blood cell count.

### Study Participants

#### Recruitment Setting

We will recruit pregnant women who meet all the inclusion criteria and do not have any of the listed exclusion criteria. In Japan, most women visit an obstetrical clinic between 5 weeks and 8 weeks of gestation. After confirming the eligibility criteria, we will register pregnant women. In this trial, a history of sPTD is defined as preterm delivery by labor pains, clinical chorioamnionitis, intrauterine infection, or histological chorioamnionitis diagnosed after preterm delivery, with or without obstetrical complications. Informed consent will be obtained from pregnant women prior to their registration. Pregnant women can review the details of this trial on the Japan Registry of Clinical Trial.

#### Inclusion Criteria

The inclusion criteria were women who had been pregnant <15 weeks, with a history of sPTD, aged 18 years to 43 years at consent, and who provided written informed consent.

#### Exclusion Criteria

The exclusion criteria included pregnant women with a history of indicated preterm birth, such as abruptio placentae, gestational diabetes mellitus, pregnancy-induced hypertension, eclampsia, HELLP (Hemolysis, Elevated Liver Enzymes, and Low Platelets) syndrome, pulmonary embolism, cerebral hemorrhage, pulmonary edema, acute fatty liver of pregnancy, placenta previa, fetal growth restriction (≤–2.0 SD), oligohydramnios, polyhydramnios, fetal diseases with chromosomal abnormalities, fetuses with multiple malformations, fetal edema, fetal dysfunction, and pregnant women with histories of sPTD for a multiple pregnancy. In addition, pregnant women with a multiple pregnancy (singleton cases after multifetal pregnancy reduction or another fetal death are also excluded), a severe physical disability, with a history of serious hypersensitivity or anaphylactic reactions caused by probiotics (including lactomin, *C. butyricum*, and amylolytic bacillus), using a medical drug or supplement including *Clostridium* spp. within 2 weeks before enrollment, with a history of cervical conization, with uterine malformation, with cervical polyps and massive genital bleeding before 10 weeks of gestation, with subchorionic hematoma and massive genital bleeding at the time of obtaining informed consent, who regularly use steroids, with diabetes mellitus, with autoimmune disease, diagnosed or treated for malignant disease at the time of informed consent (cases in which malignant disease has been completely cured may be included), with fetal morphological abnormalities at the time of informed consent, currently participating in other clinical trials or those who previously participated in a clinical trial and for whom at least 1 month has not passed since the last dose of the study drug was taken, or classified as inapplicable for this trial by the investigators are excluded.

### Study Procedures

The trial schedule is shown in Figure 2. All registered pregnant women will receive oral probiotics. The probiotics used are already available drugs including *C. butyricum* (10 mg/tablet), *Enterococcus faecium* (2 mg/tablet), and *Bacillus subtilis* (10 mg/tablet), because the probiotics containing *C. butyricum* alone are not commercially available in Japan. Probiotics are started from 10 weeks to 14 weeks and stopped at 36 weeks 6 days of gestation, late miscarriage, or sPTD. The maximum duration of administration is 188 days.

**Figure 2 figure2:**
[figure not shown]
The schedule of the Prevention of Recurrent Spontaneous Preterm Delivery by Probiotics (PPP) trial. CSS: constipation scoring system; NGS: next-generation sequencing; sPTD: spontaneous preterm delivery.

Before the initiation of probiotics, stool (for the NGS) and vaginal secretion (for the Nugent score) samples will be collected, and the Bristol Stool Form Scale (BFS; Figure 3) and the constipation scoring system (CSS: Table 1) are rated. The BFS expresses the characteristics of stool as numbers: the lower the number, the less water the stool contains and the harder it is, whereas the higher the number, the more watery and soft it is. Stool is classified into 7 levels from Type 1 to Type 7, with Type 3 to Type 5 being considered the normal range of stool, and Type 4 stool being ideal. The BFS is evaluated before and during treatment. The CSS results in a subjective score of 30 points resulting from 7 items being rated on a scale from 0 to 4 and 1 item rated on a scale from 0 to 2; the items include the number of bowel movements per week, residual bowel movements, frequency of abdominal pain, and time required for bowel movements [25]. In this trial, the CSS is a modified CSS consisting of 26 points, excluding the “duration of constipation,” and is evaluated before and during treatment. At 22 ± 2 weeks of gestation, these samples will be collected again, the questionnaire will be completed for evaluations during probiotic administration, and cervical lengths will be measured.

**Figure 3 figure3:**
[figure not shown]
The Bristol Stool Form Scale.

**Table 1 table1:** The Constipation Scoring System (total of 30 points possible).

Items evaluated	Points				
	0	1	2	3	4
Frequency of bowel movements	1-2 times per 1-2 days	2 times per week	Once per week	Less than once per week	Less than once per month
Painful evacuation effort	Never	Rarely	Sometimes	Usually	Always
Feeling of an incomplete evacuation	Never	Rarely	Sometimes	Usually	Always
Abdominal pain	Never	Rarely	Sometimes	Usually	Always
Time spent on the toilet to defecate (minutes)	<5	5-9	10-19	20-29	≥30
Type of assistance	No assistance	Stimulative laxatives	Digital assistance or enema	—^a^	—
Unsuccessful attempts to evacuate per 24 hours	0	1-3	4-6	7-9	≥10
Duration of constipation (years)	<1	1-5	6-10	11-20	≥21

^a^Not applicable.

In this trial, any treatment to prevent late miscarriage or sPTD, such as progesterone (17-alpha-hydroxyprogesterone caproate, which is used at a dosage of 125 mg and covered by the national health insurance system in Japan but is not used to prevent sPTD in the first trimester), cerclage, tocolysis, and antibiotics, could be used because there is no evidence to support their prevention of sPTD. The previously reported rate of recurrent sPTD of 22.3% in Japan [6] is presumed to be the result of these treatments.

### Endpoints

The primary endpoint is the rate of recurrent sPTD at <37 weeks of gestation. The secondary endpoints are the rate of sPTD at <34 weeks of gestation, the rate of recurrent sPTD at <28 weeks of gestation, the proportion of stillbirth, constipation (using the BFS and CSS), the ratio of intestinal *Clostridium* spp. (as measured using next-generation sequencing [NGS]), and bacterial vaginosis (using the Nugent score). In cases of sPTD, histological chorioamnionitis, or funisitis, neonatal prognosis (gestational weeks at delivery, birth weight, hospitalization in the neonatal intensive care unit [NICU], neonatal death, respiratory distress syndrome, PVL, BPD, IVH, and NEC) will be evaluated.

In this trial, to analyze the composition of the microbiota (using NGS), a stool collection brush and storage tube (Fujifilm WAKO Pure Chemicals) containing DMSO-EDTA salt solution buffer [26] was prepared, and 2 tubes were delivered to each participant. Pretreatment feces were collected in the tubes by each participant and stored under cool conditions. Posttreatment (22±2 weeks of gestation) feces were also collected. These tubes were compiled at ReLife Inc at a temperature <4°C, then transported to the Kyoto Institute of Nutrition and Pathology for analyses of the microbiota composition.

Fecal DNA was extracted using a commercial kit (QuickGene DNA tissue kit, KURABO) as described elsewhere [27]. The procedure for metagenomic 16S rRNA sequencing using Miseq (Illumina) was the same as that previously described [28]. The processing of sequencing data, including quality filtering, chimera checks, operational taxonomic unit definitions, and taxonomy assignments, was performed using QIIME1.9.1, USEARCH, and UCHIME in the same manner as previously described [28]. Alpha-diversity metrics (the Chao1 or Shannon index) were calculated using QIIME1.9.1 software. To calculate the distances between samples, beta-diversity was estimated using the UniFrac metric and visualized using a principal coordinate analysis.

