## Discussion

The reasons behind the effectiveness of probiotics or prebiotics for preventing sPTD have not been verified by meta-analysis [15-17]; potential reasons include differences between the characteristics of pregnant women at risk of sPTD, the types of probiotics or prebiotics, and initiation of their administration. In addition, the main probiotic used in previous research was *Lactobacillus* spp. This trial will examine the effects of probiotics, including *Clostridium* spp., which induce the production of Treg cells that play an important role in maintaining pregnancy [18-22]. There are a few reports that probiotics, including *Clostridium* spp., improved clinical symptoms in inflammatory bowel disease [30,31]. However, there is no report showing changes in intestinal flora or Treg cells. The proliferation of Treg cells in this study cannot be shown as direct evidence at present, and all theories remain a matter of speculation.

We are carrying out a prospective, single-arm, nonblinded, multicenter clinical trial to confirm the efficacy of oral probiotics including *C. butyricum*, *E. faecium*, and *B. subtilis* for the prevention of sPTD starting in the first trimester in pregnant women with a history of sPTD. *E. faecium* and *B. subtilis* can coexist symbiotically, and they increase their metabolic products and themselves [32]. In addition, *B. subtilis* and *C. butyricum* can coexist symbiotically, and they increase their metabolic products and themselves [33]. Therefore, these 3 bacteria, namely *E. faecium*, *B. subtilis,* and *C. butyricum*, might coexist symbiotically. Furthermore, proliferation of *C. butyricum* might further lead to the proliferation of *Clostridium* spp. in the human intestine [34,35]. Hence, the presence of these 3 types of bacteria is predicted to increase the proliferation of *Clostridium* spp. in the intestine.

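### The Clostridium ratio is sampled while women take a C. butyricum product, so a change in it cannot be split between swallowed strain, resident growth and gestation

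*Protocol article*

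**What the plan says.** All statements are from the protocol article.

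- **Endpoint (Endpoints).** A secondary endpoint is "the ratio of intestinal *Clostridium* spp. (as measured using next-generation sequencing [NGS"). It covers Clostridium species together, and the article does not set C. butyricum apart. The Abstract names it among the secondary endpoints as well.
- **Product (Study Procedures).** "The probiotics used are already available drugs including *C. butyricum* (10 mg/tablet), *Enterococcus faecium* (2 mg/tablet), and *Bacillus subtilis* (10 mg/tablet").
- **Dosing (Study Procedures).** "Probiotics are started from 10 weeks to 14 weeks and stopped at 36 weeks 6 days of gestation", or earlier at late miscarriage or sPTD. "The maximum duration of administration is 188 days".
- **Baseline sample (Study Procedures, text after Figure 2).** "Before the initiation of probiotics, stool (for the NGS) and vaginal secretion (for the Nugent score) samples will be collected". The Exclusion Criteria also rule out women who used a Clostridium product in the 2 weeks before enrollment.
- **Follow-up sample.** Endpoints states: "Posttreatment (22±2 weeks of gestation) feces were also collected". The text after Figure 2 describes the same 22±2-week visit as an assessment made while probiotics are being taken. Each woman receives two collection tubes, one for each time point.
- **Assay (Endpoints).** 16S rRNA sequencing of fecal DNA, with operational taxonomic units (OTUs) defined and assigned to taxa.
- **Expected result (Discussion).** "the presence of these 3 types of bacteria is predicted to increase the proliferation of" Clostridium species in the intestine.

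**The concern.** 16S sequencing of stool counts DNA from swallowed C. butyricum together with DNA from Clostridium already living in the gut. The two samples differ in this respect by design: the exclusion rule keeps Clostridium products away from the baseline sample, whereas the follow-up sample is taken in the middle of dosing.

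This is the only listed endpoint on the intestinal flora, and the Discussion says that no report has yet shown a change in flora with such products. A rise could therefore easily be taken as first evidence for the predicted proliferation, although the endpoint as stated cannot separate that from other explanations. The limitations in the Discussion cover the unproven link to regulatory T cells and the lack of a placebo group. They do not cover carry-over of the product into the sample.

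**Working it through.** **1. The plan's own figure.** Maximum dosing runs from 10 weeks 0 days to 36 weeks 6 days. In days: (36×7 + 6) − (10×7) = 258 − 70 = 188. This reproduces the stated 188 days.

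**2. Is the follow-up sample on treatment?** Take the earliest start as day 70 (10w0d) and the latest as day 104 (14w6d, since inclusion requires less than 15 weeks). Planned dosing ends on day 258.

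| Sample at | Day | Days on treatment (latest to earliest start) | Planned days remaining |
|---|---|---|---|
| 20w0d | 140 | 140−104 = 36 to 140−70 = 70 | 258−140 = 118 |
| 22w0d | 154 | 50 to 84 | 104 |
| 24w0d | 168 | 64 to 98 | 90 |

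Every sample in the window falls inside the planned dosing period. The Endpoints wording (Posttreatment (22±2 weeks of gestation) feces were also collected) and the description of the visit in Study Procedures do not agree; the dates support the latter.

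**3. What the total ratio contains.** Let r be the resident Clostridium ratio, s the share of all reads that come from the tablet, and c the share of tablet reads that are C. butyricum. With no change in resident flora,

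observed ratio = (1 − s)·r + s·c, so the shift is s·(c − r).

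Carry-over raises the ratio if c > r, leaves it unchanged if c = r and lowers it if c < r, because E. faecium and B. subtilis reads enter only the denominator.

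**4. Illustration.** The documents give none of r, s and c. All three are assumptions. Taking c from tablet weight, 10/(10+2+10) = 0.455, is also an assumption, since weight need not track reads.

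| c | r | s = 1% | s = 5% |
|---|---|---|---|
| 0.455 | 1% | 1.44% | 3.2% |
| 0.455 | 5% | 5.40% | 7.0% |
| 0.455 | 10% | 10.35% | 11.8% |
| 0.10 | 10% | 10.0% | 10.0% |
| 0.10 | 20% | 19.9% | 19.5% |

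Example: r = 5%, s = 1%, c = 0.455 gives 0.99×0.05 + 0.01×0.455 = 0.0495 + 0.0045 = 0.0540.

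**5. Gestation.** The baseline sample precedes the first dose, so by the table in step 2 the two samples are at least 36 days apart. With no untreated group, change over that part of pregnancy cannot be subtracted.

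**The case against.** **The hypothesis includes C. butyricum itself.** The Discussion treats growth of C. butyricum as the first step, which may then lead to growth of Clostridium species. A reader might infer that the trial sets out to show growth of other, resident Clostridium only; the text does not say so. Total Clostridium is thus a coherent on-treatment measure, and replacing it would remove part of the hypothesized effect. This stands, and it is why the endpoint should be kept and supplemented.

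**No mechanism is claimed as shown.** The Discussion predicts proliferation, calls the theories speculative, and says the trial focuses on recurrence. This stands too. The point is only about what the endpoint could support.

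**A rise is not built in.** A reader might infer that the endpoint must come out positive because women swallow Clostridium. The documents do not support that: the direction depends on c and r, which are not given, and the article states a test only for the primary endpoint, so positive has no defined meaning here.

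**The full protocol or analysis plan may tabulate C. butyricum separately.** It may, and that would answer part of the point. The pooled endpoint, the sampling time and the label are nevertheless fixed in this article, and no separate tabulation would supply an off-treatment sample or a control.

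**The timing and the missing control are disclosed.** Study Procedures makes clear that the visit falls during dosing, and the Discussion lists the lack of a placebo group. The label in Endpoints is therefore a wording slip, but it still needs reconciling.

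**Conclusion.** The point holds in a limited form. Under the planned schedule, the only follow-up stool sample comes after 36 to 98 days of dosing with a product that contains C. butyricum, with 90 to 118 planned days still to run. With one pooled ratio, no off-treatment sample and no control, a change cannot be divided between passage of the swallowed strain, growth of resident Clostridium and gestational change. By itself it cannot support the predicted proliferation.

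The size of the carry-over is unknown. The illustrated effects run from a slight fall (20% to 19.5%) to a tripling of a low ratio (1% to 3.2%), all on assumed inputs. The timing rests only on the stated dosing and sampling windows and on women following the schedule. The primary endpoint and the sample size do not depend on any of this. It is an inexpensive improvement to a secondary endpoint, not a threat to the trial's main conclusion.

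**What to change.** 1. Keep the total Clostridium ratio as the stated secondary endpoint. All 345 women are already registered, so replacing it now would raise its own reporting question.
2. Add a tabulation that excludes OTUs assigned to C. butyricum, specified before the paired sequencing results are examined. State whether the excluded reads also leave the denominator.
3. Report C. butyricum reads separately as a marker of exposure.
4. In Endpoints, call the 22±2-week sample on treatment, in line with Study Procedures.
5. Describe the within-woman change as a change during dosing and gestation, not as an effect of the product on resident flora.

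**Cost.** Items 2 and 3 re-tabulate output that the sequencing pipeline already assigns to taxa, and the other items are wording. No sample or visit is added. There are two limits. 16S sequencing may not fully separate C. butyricum from close relatives, so some resident reads may be removed or some product reads retained. The split also cannot tell passage of the swallowed strain from its multiplication in the gut, nor remove gestational change; item 5 is needed for that reason.
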